## Abstract

**Background:**

High blood pressure is the leading cause of cardiovascular disease worldwide. The prevalence of high blood pressure is steadily rising as the population grows amongst older adults with the ageing population. Therapeutical treatments are widely available to decrease blood pressures, in addition to many lifestyle options, such as dietary changes and exercise. There is a marked preference amongst patients, as reiterated by Hypertension Canada, for more research into non-therapeutic methods for controlling blood pressure or to reduce the burden of taking many pills to control high blood pressure. Indeed, effective options do exist, especially with diet, specifically decreasing sodium and increasing potassium intake. Current public health outreach primarily focusses on sodium intake, even though potassium intake remains low in the Western world. Excellent data exist in published research that increasing potassium intake, either via dietary modification or supplements, reduces blood pressure and reduces risk of cardiovascular outcomes such as stroke. However, the advice most often provided by medical professionals is to ‘eat more fruits and vegetables’ which has little impact on patient outcomes.

**Methods:**

We propose to do a clinical trial in two stages with an adaptive trial design. In the first stage, participants with high blood pressure and proven low potassium intake (measured on the basis of a 24-h urine collection) will get individually tailored dietary advice, reinforced by weekly supportive phone/email support. At 4 weeks, if there has not been a measured increase in potassium intake, participants will be prescribed an additional potassium supplement. Testing will be conducted again at 8 weeks, to confirm the efficacy of the potassium supplement. Final measurements will be planned at 52 weeks to observe and measure the persistence of the effect of diet or additional supplement. Concurrent measurements of sodium intake, blood pressure, participant satisfaction, and safety measures will also be done.

**Discussion:**

The results of the study will help determine the most effective method of increasing potassium intake, thus reducing blood pressure and need for blood pressure-lowering medicines, and at the same time potentially increasing participant satisfaction. The current guidelines recommend changes in diet, not a potassium supplement, to increase potassium intake; hence, the two-stage design will only add supplements if the most rigorous dietary advice does not work.

**Trial registration:**

This study has been registered on ClinicalTrials.govNCT03809884. Registered on January 18, 2019

**Supplementary Information:**

The online version contains supplementary material available at 10.1186/s13063-022-06071-9.

## Background

Hypertension is the leading cause of death and disability in Canada and globally. Apart from a wide choice of pharmacological agents, multiple lifestyle modifications, in particular an increase in potassium intake by diet or as a supplement, have been shown to be efficacious in reducing blood pressure (BP) [1–3]. An increase in dietary potassium is recommended by the World Health Organization [4], the American Heart Association/American College of Cardiology [5], and Hypertension Canada [6, 7]. Despite this, potassium intake remains stubbornly low in western world, including in Canada. Similar to the relative slowness in behaviour change with reducing sodium, the reason why trials of efficacy may not have translated into change is that the interventions in the trials of dietary modification have not been feasible (including supervised intake of meals and/or provision of meals) to be used in clinical practice. In contrast to behavioural modification required for increasing potassium intake in food, namely change in dietary habits, addition of potassium supplements might be an easy to implement alternative [8, 9]. The advocacy of potassium supplements has not made it into any guidelines despite robust data of their efficacy and the public enthusiasm for consuming health supplements.

Increasing potassium intake itself is a robust, but often overlooked, means of decreasing BP [9, 10]. The effect of increasing potassium on BP is seen at low as well as high sodium intake, for example in the Dietary Approach to Stop Hypertension Sodium (DASH Sodium) trial, the effect of the potassium rich DASH diet was − 5.0/− 2.5 mm Hg at high sodium intake and − 2.2/− 1.0 at low sodium intake [11] . Increasing dietary potassium intake has an inverse association not just with BP but can impact cardiovascular disease. Systematic reviews and meta-analyses of randomized controlled trials on the effect of increased potassium intake on BP show significant decreases in systolic and diastolic BP with increased potassium intake [8–13]. Globally, hypertension is the leading risk factor for mortality, accounting for 13% of death, and also being the leading cause of disability worldwide, according to the Global Burden of Disease studies [14–16]. Research on lifestyle habits to reduce blood pressure, without involving pharmacotherapy has been identified as a top research priority by Hypertension Canada [1].

Advocating high potassium intake either in the form of diet or as use of a potassium supplement to the diet may pose a risk in certain populations. However, except in individuals with advanced chronic kidney disease or other conditions impairing renal potassium handling, adaptive mechanisms are triggered that allow for excretion of excess potassium in the urine [17–19]. Thus, increasing potassium intake, as part of the diet or as a supplement, has little adverse effects in most populations [9, 13]. In this adaptive trial, we will test the effectiveness of dietary counselling, followed by additional potassium supplementation in those in whom dietary counselling is ineffective. The objective of this study is to determine an effective strategy for increasing potassium intake in hypertensive individuals with low potassium intake.

## Methods

### Study design and setting

The study design is a single-centre, single arm clinical trial, with an adaptive design of two possible sequential interventions. For the dietary advice, this is outside the phases which apply to pharmacological trial regulatory description. The potassium supplement aspect could be considered as a phase 2, since, though approved for other indications, they have not been approved for hypertension. Focused and individualized dietary counselling to increase potassium intake will be the initial intervention amongst hypertensive individuals with low potassium intake. The aim of the study is to find the most effective intervention to increase potassium intake in this population. Since diet is the only recommendation in current clinical practice guidelines, this will be the initial intervention. Only in participants who do not achieve an increase in potassium intake, as measured on the basis of her 24-h urine potassium, as described below, will a potassium supplement be added. From a safety perspective, this was thought to be the most suitable study design. A comparison of a potassium supplement with a diet might result in a change in diet in patients randomized to a supplement, with possible safety issues in terms of hyperkalemia. Hence, the study design is a two-stage intervention, of dietary counselling, with the second stage of supplement only added to those in home the dietary counselling has been insufficient in increasing potassium intake (Figs. 1 and 2).

**Fig. 1 Fig1:**
[figure not shown]
Stage 1 study period content for all participants (stage 1), including the schedule of enrollment, interventions, and assessments for the Diet or Additional Supplement to Increase Potassium study

**Fig. 2 Fig2:**
[figure not shown]
Stage 2 study period content for participants who failed stage 1, including the schedule of enrollment, interventions, and assessments for the Diet or Additional Supplement to Increase Potassium study

This study and patient recruitment will take place in a referral hypertension clinic at a tertiary care teaching hospital. Patients with difficult to control hypertension are referred to this clinic, and all patients undergo evaluation of their sodium and potassium intake with a 24-h urinary collection. The study coordinator will obtain written informed consent and to ensure that all necessary information is obtained. During the consent process, the study coordinator will ensure that there are no overtures of coercion, duress, or undue incentive. On the consent form, participants will also be asked if they agree to use their data should they choose to withdraw from the study.

### Study population and timeline

In this trial, all patients with low dietary potassium intake will be eligible for enrolment. The study coordinator will screen patient for eligibility and obtain informed consent. Patients known to be at risk for hypokalaemia or hyperkalaemia will be excluded. The estimated duration for this study is 4 years.

Inclusion criteria:

(1) Hypertension (either on treatment, any level of BP; or not on treatment with an ambulatory blood pressure monitoring (ABPM) with daytime systolic blood pressure (SBP) > 140 or diastolic blood pressure (DBP) > 90)

(2) Aged 18 and greater

(3) 24-h urine potassium < 60 mmol

Exclusion criteria:

(1) Serum potassium < 3.3 or > 5.1 mmol/L

(2) Glomerular filtration rate (GFR) < 45 ml/min/1.73 m^2^

(3) Primary hyperaldosteronism

(4) Pregnancy

(5) Psychiatric disorder which, in the opinion of the investigator, would interfere with the study, or inability to give consent

(6) Severe liver disease

(7) Metabolic alkalosis (HCO_3_ > 32 mmol/L)

(8) Exclude patients who need to be started on renin-angiotensin-aldosterone blockade in the next 3 months

(9) Gastrointestinal disorder (delayed gastric emptying, dysphagia, gastric/duodenal/oesophageal ulcers)

### Interventions

#### Stage 1: Counselling

All enrolled patients will undergo a 1:1 counselling with a registered dietitian (with possible inclusion of family members, as appropriate). The dietitian will undertake an assessment of the comorbidities (e.g. diabetes), dietary intake, and dietary habits (e.g. eating out, food preparation, socio-cultural aspects) and provide an individually tailored strategy to increase potassium in the diet. Secondly, on a weekly basis, the dietitian will contact the patient by telephone or electronically (as preferred by the patient) to reinforce the advice and provide support and advice as necessary. Patients who are successful in increasing potassium to desirable levels at 4 weeks (see the “Outcomes” section) will continue to have follow-up for one more year.

The counselling will be individualized and focused on addition of food ingredients or items to increase potassium intake, rather than a complete overhaul of the participant lifestyle.

#### Stage 2: Potassium supplementation

Patients who are not able to successfully increase their potassium intake at 4 weeks with dietary counselling will be enrolled into stage 2. They will receive oral potassium supplementation in the form of 50 to 100 mmol of potassium citrate (25 to 50 ml of the liquid elixir based on the achieved 24-h urinary potassium). For those whose urinary 24-h potassium remains < 60 mmol/day, the dose of the supplement will be 100 mmol/day, and for those whose 24-h urinary potassium is between 60 and 90 mmol/day, the dose will be 50 mmol/day. In the DASH trial, the diet itself provides 120 mmol/day of potassium; however, the average measured 24-h urinary potassium was 2757 mg/day (~ 71 mmol/day). Hence, we are aiming for a higher dose of supplement to achieve the target outcome.

This dose of potassium is well tolerated in hypertension (reported adverse events, at < 1% frequency and not different from placebo, are change in bowel habits, belching and flatulence, and abdominal cramps with the current wax matrix-based and microencapsulated or coated microcrystal-containing preparations with extended release characteristics) [9, 20]. There are no reports of hyperkalemia reported in trials using this dose in a similar population [9, 13]. Potassium at this dose and formulation has excellent (> 90%) bioavailability [20]. This dose of potassium also should be effective in increasing urinary potassium to desired levels. There is also no comparator in this study since it is not a randomized controlled trial. Since potassium is well tolerated in hypertension, there will be no special criteria for discontinuing or modifying allocated interventions.

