### Outcomes

The primary outcome will be a successful increase in potassium intake to > 90 mmol/day as estimated from the 24-h urinary sample at 4 weeks. The secondary outcomes are persistence of increase in potassium intake (to > 90 mmol/day) at 1 year. For examination of safety, the following outcomes will be specifically examined: hyperkalemia (as defined as a serum potassium > 5.1 mmol/L) at 4 weeks after initiation of dietary counselling, at 1 and 4 weeks after starting potassium supplements, 1 week after dose escalation/dispensing, and at 12 months in everyone and gastrointestinal side effects (change in bowel habits, belching and/or flatulence; abdominal pain or cramps). Additional patient-reported adverse effects will also be measured and reported. Serious adverse events will be captured and reported as per regulatory requirements.

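### Stage 2 disclaims special stopping or dose-change criteria, so a serum potassium above 5.1 mmol/L, the trial's own entry limit, does not bar starting or continuing the supplement

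*Protocol article*

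**What the plan says.** Under Stage 2: Potassium supplementation, the protocol article reasons from good tolerability in hypertension that "there will be no special criteria for discontinuing or modifying allocated interventions". It adds: "There are no reports of hyperkalemia reported in trials using this dose in a similar population".

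The same section sets the dose by urine: "the dose of the supplement will be 100 mmol/day, and for those whose 24-h urinary potassium is between 60 and 90 mmol/day". Participants who remain under 60 take the higher amount, and the 60 to 90 group takes 50 mmol/day. Serum potassium plays no part in stage 2 entry or in the dose.

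Elsewhere serum potassium is treated as a safety variable:
- Study population and timeline lists as an exclusion "Serum potassium < 3.3 or > 5.1 mmol/L".
- Outcomes names as a safety outcome "hyperkalemia (as defined as a serum potassium > 5.1 mmol/L", assessed after 4 weeks of counselling, 1 and 4 weeks after the supplement starts, 1 week after an escalation or dispensing, and at 12 months.
- Measurements describes the 1-week tests as an added safety precaution.
- Study design and setting gives possible hyperkalemia as a reason for not comparing supplement with diet, since people given a supplement might change their diet as well.

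**The concern.** The trial chose one serum potassium value as too high for entry and as its definition of harm, and it schedules tests to find that value during treatment. It then declines to say what follows when the value is found. The supplement is the intervention that raises potassium, and it is given after counselling meant to raise potassium through food. That is the combination the design section itself flags.

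Participant safety is at stake first. Consistency comes second: without a pre-stated response, two participants with the same raised result may be handled differently. The primary proportion at 4 weeks of counselling is not affected, because it is fixed before any supplement is given.

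**Working it through.** The point concerns a rule, so most of the check is a comparison of text. The plan gives no figure to reproduce.

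**1. Threshold.** Entry limit (Study population and timeline): above 5.1 mmol/L. Hyperkalemia definition (Outcomes): above 5.1 mmol/L. They are identical.

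**2. Tests and actions for a stage 2 participant** (Outcomes; Measurements):
- Week 4 of counselling, before the supplement: tested, no action stated.
- 1 week and 4 weeks after starting: tested, no action stated.
- 1 week after each escalation or re-dispensing: tested, no action stated.
- 12 months: tested, no action stated.

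Minimum count: 1 before the supplement + 2 on it (weeks 1 and 4) = 3. If the supplement continues to 12 months, which the abstract and the re-dispensing visits suggest but the article does not say outright, the count is 1 + 3 = 4. Each escalation or re-dispensing adds one.

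**3. Following the rule as written.** Take a participant who entered with acceptable serum potassium and at week 4 has serum potassium above 5.1.
- Urinary potassium below 60 mmol/day: enters stage 2 at 100 mmol/day.
- Urinary potassium 60 to 90 mmol/day: enters stage 2 at 50 mmol/day.
- The serum value alters neither step. If it first exceeds 5.1 on the supplement, the stated position is still that no special criterion applies.

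**4. Do other provisions supply a response?**
- Entry exclusions ("Patients known to be at risk for hypokalaemia or hyperkalaemia will be excluded"; "Glomerular filtration rate (GFR) < 45 ml/min"; "Exclude patients who need to be started on renin-angiotensin-aldosterone blockade in the next 3 months"): these lower the expected rate but operate at enrolment.
- Adverse events: events are followed until they resolve or settle. No dose action is given.
- Data safety monitoring board: prompt notice is triggered by a possibly related serious adverse event, not by a potassium value. Adverse effects are otherwise reviewed in periodic reports.

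None gives a participant-level response to a raised result.

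**5. Scale of the remedy, on an assumption.** The documents give neither the size of stage 2 nor the share above 5.1. Stage 2 cannot exceed the 120 enrolled. If 1% to 5% (assumed) exceeded the level:
- 0.01 × 120 = 1.2 people
- 0.05 × 120 = 6 people

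If every one of them would otherwise have succeeded, the two-stage success proportion falls by at most the share held. That is 1 to 5 percentage points when all 120 enter stage 2, and proportionately less when fewer do.

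**The case against.** The strongest reply is that the sentence disclaims only *special* criteria. The trial is open label in a referral hypertension clinic, investigators ask about adverse events at each visit, and the timing of the 1-week tests suggests that someone will look at them. That much stands. A reader might infer that the protocol directs 100 mmol/day for a participant known to be hyperkalemic, or forbids stopping. The text does neither; it only fails to bar it.

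A second reply is that this is a condensed article, and laboratory action levels normally sit in the full protocol, which is said to be available on request. For a bare omission that would settle the matter. Here the article makes a positive statement and gives a reason for it, so a hold rule in the full document would conflict with the published text.

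Third, the authors have evidence for a low rate, and an entry limit need not be a stopping limit. Both are fair. Evidence that an event is rare does not say what to do when it occurs, and the remedy leaves room for a different level. The adverse-event frequency below 1% quoted in the same section lists gastrointestinal complaints with extended-release preparations, while this trial uses a liquid elixir. It therefore says little about serum potassium here.

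Two further inferences should be resisted. A reader might see a contradiction between the disclaimer and the mentions of dose escalation. Since the intervention is defined as a range of 50 to 100 mmol, a step within it can coexist with the sentence; at most the trigger is unstated. A reader might also make much of the 3-month limit in the renin-angiotensin-aldosterone exclusion against 52 weeks of follow-up. No section says such drugs will be started later, or how often, so the point does not rest on it.

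**Conclusion.** The concern holds in a limited form and should be fixed. The stated rule does not bar starting or continuing 50 to 100 mmol/day after a serum potassium that the trial itself treats as disqualifying and as hyperkalemia. At least three scheduled results per stage 2 participant carry no stated response, or four if supplementation runs to 12 months.

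The conclusion rests on the article's affirmative sentence and on the absence of any response in the sections shown. It does not rest on an assumed frequency: the expected rate is low, and the range of 1 to 6 people is illustrative. A reader might go further and infer that participants will be harmed or that the success estimates are biased. The documents support neither, since clinical judgement remains available and no estimate is shown to be wrong.

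**What to change.** Replace the sentence in the stage 2 section with a rule along these lines: if a scheduled serum potassium exceeds 5.1 mmol/L, or another level agreed in advance with the DSMB, the supplement is not started or escalated; if already being taken, it is held or reduced pending a repeat test. State what the repeat result must show before the supplement is started or resumed, and that clinical judgement may be stricter than the rule.

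Keep participants who are held, reduced or never started in the analysis of the two-stage success proportion and of 1-year persistence, scored on their measured urinary potassium.

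The cost is a wording change agreed with the DSMB, an occasional unscheduled repeat test, and a possible small fall in the two-stage success proportion. The routine tests are already scheduled, so the rule needs no extra visits beyond those repeats.

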### Outcomes

The primary outcome will be a successful increase in potassium intake to > 90 mmol/day as estimated from the 24-h urinary sample at 4 weeks. The secondary outcomes are persistence of increase in potassium intake (to > 90 mmol/day) at 1 year. For examination of safety, the following outcomes will be specifically examined: hyperkalemia (as defined as a serum potassium > 5.1 mmol/L) at 4 weeks after initiation of dietary counselling, at 1 and 4 weeks after starting potassium supplements, 1 week after dose escalation/dispensing, and at 12 months in everyone and gastrointestinal side effects (change in bowel habits, belching and/or flatulence; abdominal pain or cramps). Additional patient-reported adverse effects will also be measured and reported. Serious adverse events will be captured and reported as per regulatory requirements.

### Blinding

The trial design is open label, given that behavioural change is difficult to blind. However, numerous safeguards will be in place to minimize actual bias in the data collected.

#### Blinded assessment of outcomes

The primary outcome in this trial is a change in potassium intake, as measured by 24-h urinary potassium. This is an objective measure, however, and the laboratory personnel measuring the values will not be aware of which intervention is ongoing when they perform the measurement.

#### Ascertainment and follow-up plan

In order to minimize ascertainment bias, all patients, irrespective of the group, will have similar measurement schedule. Nevertheless, we will study the frequency of loss to follow-up and reasons thereof.

### Measurements

The dietary intake of potassium will be assessed using 24-h collection of urine. There is a very close relationship overall between urinary potassium excretion and dietary potassium intake. There is a circadian variation [21] (more potassium excretion in the day than at night) which will be overcome with a 24-h urine collection. Twenty four-hour urinary sodium and creatinine (to assess for accuracy of collection) will also be measured for all participants at baseline, 4 weeks, and 52 weeks (end of study). In addition, participants who enrol into stage 2 will have an additional 24-h urinary collection and set of measurements at 4 weeks after initiation of the potassium supplement/dose escalation. Blood will also be collected at the same time points for measurement of kidney function and electrolytes (creatinine, sodium, potassium, total CO_2_, chloride). As an additional safety measure, serum potassium will be measured 1 week after starting potassium supplementation, 1 week after dose escalation, and 1 week post each re-dispensing visit. Blood pressure will be measured using automated oscillometric measurements and 24-h ambulatory monitoring. Additional assessment of adherence to supplement (apart from 24-h urine measures) will be made on the basis of returned pills/bottles. Patients satisfaction will be assessed using a simple 3 question survey (see supplementary material). Furthermore, all collected samples will be sent over to the laboratory for analyses. Any leftover samples will be discarded as medical wastes. There are no plans for subsequent or ancillary analyses for the future studies.

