### Sample size and analytical plan

The study goal is to estimate the success rate of the dietary intervention, as well as the success rate of the two-stage approach. Dietary counselling alone will not exceed this degree of increase which was seen with supervised intake and meal provision, but there are no robust data to support an estimate of its effect. However, potassium supplementation at the dose proposed would very likely result in achieved potassium intake of > 90 mmol/day in all participants. A sample size of 100 participants will allow us to able to estimate both success rates to within a margin of error of at most 5%. At 4 weeks, there should be little loss to follow-up; however, we estimate this to be about 20% to be conservative. Thus, this trial will enrol 120 participants. Furthermore, there are no plans for additional analyses including subgroup. Multiple imputation will be done for any missing data.

The primary outcome is a simple proportion of the participants who are able to achieve an increase in potassium intake. Secondary outcomes of the proportion of participants with persistent adequate potassium intake at 52 weeks, and safety outcomes, will also be reported as proportions. For the secondary outcomes of change in sodium, potassium, and blood pressure, the mean differences will be calculated and reported, and a paired *t*-test will be used to compare for statistical significance. There will be no interim analysis.

The proportions will be summarized as absolute numbers and percentages. Continuous outcomes will be reported as mean (and 95% confidence intervals). A *p* value of < 0.05 will be used for the paired comparisons of the continuous outcomes (i.e. secondary outcomes of change in sodium, potassium and blood pressure).

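### Week-4 failures who never start the supplement have no scheduled stage 2 outcome, and imputing them from supplement takers can overstate the two-stage success rate

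*Protocol article*

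**What the plan says.** The section on sample size and analysis states the aim in these words: "The study goal is to estimate the success rate of the dietary intervention, as well as the success rate of the two-stage approach". It sizes the trial for both rates, with a stated margin of at most 5% at 100 participants, and prescribes multiple imputation for missing data.

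Entry to stage 2 is automatic on failing stage 1: "Patients who are not able to successfully increase their potassium intake at 4 weeks with dietary counselling will be enrolled into stage 2" (Stage 2: Potassium supplementation). Refusal is not mentioned.

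Under Measurements, everyone has urine collections at baseline, 4 weeks and 52 weeks. Those who enter stage 2 get one more, described there as "additional 24-h urinary collection and set of measurements at 4 weeks after initiation of the potassium supplement/dose escalation". The Methods part of the Abstract gives a fixed time instead: "Testing will be conducted again at 8 weeks, to confirm the efficacy of the potassium supplement".

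The Outcomes section defines the primary outcome as a "successful increase in potassium intake to > 90 mmol/day as estimated from the 24-h urinary sample at 4 weeks" and the secondary outcome as persistence at 1 year. It gives two-stage success no assessment time and does not say which collection decides it.

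Dose escalation appears under Measurements and in the safety schedule under Outcomes ("1 week after dose escalation/dispensing, and at 12 months in everyone"). The stage 2 section sets the dose from the achieved urinary potassium (for example, "For those whose urinary 24-h potassium remains < 60 mmol/day, the dose of the supplement will be 100 mmol/day"), describes no escalation step, and sets no specific criteria for changing the interventions.

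**The concern.** The two-stage success rate describes a strategy: counsel everyone, then offer a supplement to those who fail. It belongs to everyone who enters, and not taking up the second step is one way for the strategy to fail.

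The stage 2 measurement is tied to treatment behaviour. A person who never starts has no date from which to count 4 weeks. Their stage 2 outcome is then missing because the strategy was not taken up, yet the stated remedy treats it like any other missing value. The observed stage 2 values all come from people who started, and the protocol expects essentially all of them to succeed. Imputation from that pool largely replaces non-uptake with success.

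This also sits badly with the Ascertainment and follow-up plan section, which promises everyone a comparable measurement schedule in order to limit ascertainment bias. What is at stake is one of the two rates for which the trial was sized.

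**Working it through.** **Yardstick.** The protocol gives no figure for refusal or for this bias. Its only related figure is the margin of at most 5 points at n = 100. The 95% half-width is 1.96 × √(p(1−p)/n):

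- p = 0.5: 1.96 × √(0.25/100) = 9.8 points
- p = 0.9: 1.96 × √(0.09/100) = 5.9 points
- p = 0.93: 1.96 × √(0.0651/100) = 5.0 points

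The stated margin is therefore met only for rates of about 0.93 or more (or 0.07 or less). That is a separate matter and no evidence for this point. The 5 points serve here only as the protocol's own measure of tolerable error.

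**Inputs, all assumptions**

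- s = success at week 4: 0.2 to 0.4
- q = stage 2 success among those who start: 0.7 to 0.9
- d = share of week-4 failures who never start: 0.05, 0.10 or 0.20

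**Formulas**

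- Never-starters counted as not successful: s + (1−s)(1−d)q
- Never-starters imputed like takers: s + (1−s)q
- Difference: (1−s)·d·q

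**Worked case per 100 enrolled, with s = 0.2, q = 0.9, d = 0.10.** There are 20 successes and 80 failures at week 4. Of the 80, 8 never start and 72 do; 72 × 0.9 = 64.8 succeed.

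- Counted as not successful: 20 + 64.8 = 84.8%
- Imputed like takers: 84.8 + 8 × 0.9 = 92.0%
- Overstatement: 7.2 points

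**Range**

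| d | lowest (s = 0.4, q = 0.7) | highest (s = 0.2, q = 0.9) |
|---|---|---|
| 5% | 0.6 × 0.05 × 0.7 = 2.1 points | 0.8 × 0.05 × 0.9 = 3.6 points |
| 10% | 0.6 × 0.10 × 0.7 = 4.2 points | 0.8 × 0.10 × 0.9 = 7.2 points |
| 20% | 0.6 × 0.20 × 0.7 = 8.4 points | 0.8 × 0.20 × 0.9 = 14.4 points |

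**Break-even.** The shift reaches 5 points when d = 0.05/((1−s)q): 0.05/0.72 = 6.9% at one end and 0.05/0.42 = 11.9% at the other.

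**Sensitivity.** These figures take every never-starter as a failure. If a share q₀ of them would exceed the threshold on diet alone, the difference shrinks to (1−s)·d·(q−q₀).

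**The case against.** The strongest reply is that this is a condensed article. The stage 2 schedule figure is not shown, the full protocol exists separately, and the imputation model belongs in an analysis plan. A good model might treat never-starters differently, tolerability is expected to be good, and the primary outcome is untouched.

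Part of this stands. The bias is a risk, not a certainty, and its size is assumed. At 5% never-starters it stays below 5 points. But the two rules that create the risk are both written in the article. A better imputation model helps little, because under the stated schedule no never-starter has a stage 2 value from which to learn. The 52-week value could inform the model, but its relation to the stage 2 value would be learned from takers.

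A reader might infer more than the documents support:

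- **That people who stop the supplement also lack an outcome.** They have an initiation date, so a collection is due, and nothing limits it to those still taking the supplement.
- **That never-starters drop out of the denominator.** The protocol plans imputation, not a complete-case analysis. In the worked case the latter would give 84.8/92 = 92.2%, close to the imputed figure, but it is not what is planned.
- **That escalated participants get a second try.** The text speaks of one additional collection and never says that a later value replaces a failed one. If escalation is part of the strategy, counting its result is not bias in itself. The fault is that no rule is given.
- **That the Abstract and the Measurements section flatly conflict on timing.** Stage 2 follows the week-4 test, so 4 weeks after initiation is nominally week 8. They part only for late starts or escalation.

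It is also fair to say that a rigid week-8 test would catch late starters after less than 4 weeks on the supplement. For that reason the fix asks for a nominal time.

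**Conclusion.** The point holds for week-4 failures who never start the supplement. They have no scheduled stage 2 outcome before week 52, and the stated imputation would fill the gap mainly from takers. This can overstate the two-stage rate by roughly 4 to 7 points if one in ten week-4 failures never starts. That rests on the assumed success rates, on imputation that does not separate never-starters, and on never-starters not exceeding the threshold by diet alone. With few refusals the effect is small; above about 7–12% it exceeds the protocol's own 5-point margin.

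The missing assessment time for two-stage success and the undefined dose escalation are gaps in definition. Neither shows by itself that the rate is inflated. The change is worth making because it is cheap and protects a stated study goal.

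**What to change.** 1. Schedule the stage 2 collection for every week-4 failure at nominal week 8, as the Abstract already says, whether or not the supplement was started or continued.
2. Use all enrolled participants as the denominator of the two-stage rate.
3. Count week-4 failures who never start and give no sample as not successful, and limit multiple imputation to other missing data.
4. State in advance which collection defines two-stage success.
5. Reconcile the mentions of dose escalation under Outcomes and Measurements with the stage 2 section, which has no such step. No clinical rule is proposed here.

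The cost is a change of wording, a few extra urine collections of a type already planned, and a slightly lower reported rate.
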